## **7.2 Flutamide (NSC# 147834)**

### **7.2.1 Description:**

Flutamide is a substituted anilide. It is a fine, light, yellow powder, insoluble in water but soluble in common organic solvents such as aromatic or halogenated hydrocarbons. Its concentration in plasma can be determined by gas chromatography. Flutamide is a non-steroid anti-androgen that is metabolized into a hydroxylated derivative which effectively competes with the hydrotestosterone for androgen receptor sites.

### **7.2.2 Supply:**

Flutamide is commercially available.

### **7.2.3 Storage:**

Flutamide is supplied as 125 mg capsules. Flutamide should be stored at temperatures ranging from 2°-30°C (36°-86°F) and be protected from excessive moisture.

### **7.2.4 Administration:**

The drug is administered orally at a dose of two 125 mg capsules three times a day for a total daily dose of 750 mg beginning 2 months prior to radiotherapy and continuing throughout radiotherapy. Administration of flutamide will be terminated on the last day of radiotherapy or on day 112, whichever occurs first. During radiotherapy interruptions the drug will be continued. Administration of the drug will be suspended only if there is an apparent or suspected reaction to the drug.

### **7.2.5 Toxicity: (11/13/00)**

The reported side effects of treatment include diarrhea and anemia. A high percentage of patients treated with flutamide alone developed gynecomastia within 2-8 months. There have been post-marketing reports of hospitalization, and, rarely, death due to liver failure in patients taking flutamide. Evidence of hepatic injury included elevated serum transaminase levels, jaundice, hepatic encephalopathy, and death related to acute hepatic failure. The hepatic injury was reversible after prompt discontinuation of therapy in some patients. Approximately half of the reported cases occurred within the initial 3 months of treatment with flutamide.

### 7.2.6 Dose Modification Schedule: (11/13/00)

If gastrointestinal disturbances (*cramps, diarrhea*) occur prior to initiation of radiotherapy, flutamide will be withheld until the side effects subside and then reintroduced at a dose of 250 mg/day increasing the dose (*at 3 day intervals*) to 500 mg/day then 750 mg/day as tolerated.

If gastrointestinal disturbances occur after administration of radiotherapy it might be difficult to identify their cause. However if severity of diarrhea exceeds the level commonly observed during pelvic irradiation the toxicity will be ascribed to Flutamide and the drug will be permanently discontinued.

ALT will be measured pretreatment, then monthly during oral antiandrogen therapy. If ALT increases  $\geq 2 \times$  upper institutional limit of normal, flutamide must be discontinued. RTOG Headquarters must be notified.

## 7.3 Leuprolide (1/8/99)

### 7.3.1 Description

Leuprolide acetate is a synthetic nonapeptide analog of naturally occurring gonadotropin-releasing hormone (*GnRH or LH-RH*). The analog possesses greater potency than the natural hormone. Leuprolide acetate, an LH-RH agonist, acts as a potent inhibitor of gonadotropin secretion when given continuously and in therapeutic doses. Animal and human studies indicate that following an initial stimulation, chronic administration of leuprolide acetate results in suppression of ovarian and testicular steroidogenesis. This effect is reversible upon discontinuation of drug therapy. Administration of leuprolide acetate has resulted in inhibition of the growth of certain hormone dependent tumors (*prostatic tumors in Noble and Dunning male rats and DMBA-induced mammary tumors in female rats*) as well as atrophy of the reproductive organs.

In humans, administration of leuprolide acetate results in an initial increase in circulating levels of luteinizing hormone (*LH*) and follicle stimulating hormone (*FSH*), leading to a transient increase in levels of the gonadal steroids (*testosterone and dihydrotestosterone in males, and estrone and estradiol in premenopausal females*). However, continuous administration of leuprolide acetate results in decreased levels of LH and FSH. In males, testosterone is reduced to castrate levels. In premenopausal females, estrogens are reduced to postmenopausal levels. These decreases occur within two to four weeks after initiation of treatment, and castrate levels of testosterone in prostatic cancer patients have been demonstrated for more than five years.

### 7.3.2 Supply

Leuprolide is commercially available as either 7.5 mg (*one month*), 22.5 mg (*three month*), or 30 mg (*four month*) depot injections. Each kit contains a vial of sterile lyophilized microspheres, which is leuprolide incorporated in a biodegradable polymer of polylactic acid.

### 7.3.3 Storage

The vial of leuprolide and the ampule of diluent may be stored at room temperature.

### 7.3.4 Administration (11/13/00)

Leuprolide will be administered (*7.5 mg IM monthly x 4 or 22.5 mg IM x 1 plus 7.5 mg IM x 1*). As with other drugs administered by injection, the injection site should be varied periodically. Incorporated in a depot formulation, the lyophilized microspheres are to be reconstituted and administered every three months as a single intramuscular injection.

### 7.3.5 Toxicity

In the majority of patients testosterone levels increased above baseline during the first week, declining thereafter to baseline levels or below by the end of the second week of treatment. The most common side effect of Leuprolide is vasomotor hot flashes; edema, gynecomastia, bone pain, thrombosis, and GI disturbances have occurred.

Potential exacerbations of signs and symptoms during the first few weeks of treatment is a concern in patients with vertebral metastases and/or urinary obstruction or hematuria which, if aggravated, may lead to neurological problems such as temporary weakness and/or paresthesia of the lower limbs or worsening of urinary symptoms.

## 7.4 Adverse Reaction Reporting (4/1/95, 1/8/99)

7.4.1 The following ADR's attributed to commercial agent(s) should be reported to the Investigational Drug Branch, Cancer Therapy Evaluation Program, within 10 working days:

7.4.1.1 Any ADR which is both serious (*life threatening, fatal*) and unexpected.

7.4.1.2 Any increased incidence of a known ADR which has been reported in the package insert or the literature.

7.4.1.3 Any death on study if clearly related to the commercial agent(s).

**7.4.1.4** The ADR Report should be documented on Form FDA 3500 and mailed to:

Investigational  
Drug Branch Box  
30012  
[name]  
[contact] (24 hours)  
[contact]

## **8.0 SURGERY**

### **8.1 Pelvic Lymph Node Dissection**

**8.1.1** The pelvic lymph node dissection (*PLND*) should be done in order to accurately provide surgical/pathological staging for each patient randomized to RTOG 94-08. As suggested by previous RTOG protocols, surgical pathological staging has a dramatic impact on sub- stratification of patients and affects eventual outcome and survival statistics. The method by which the PLND is done, whether by a standard open procedure or by laparoscopic techniques, should not bias the study in any way. Both techniques of PLND, open and laparoscopic, are comparable in the literature in terms of the number of nodes removed and the incidence of positive nodes. There is an advantage to the laparoscopic PLND in that it lowers the length of stay in hospital and speeds patient convalescence and minimizes patient pain. It is an ideal form of surgical/pathological staging prior to definitive radiotherapy, allowing the radiotherapist to concentrate the fields on the prostate and periprostatic tissue and spare the pelvic lymph nodes (*assuming the dissection was negative for malignancy*). Laparoscopic PLND may not be available at all institutions participating in RTOG 94-08, and therefore open surgical PLND is also acceptable.

### **8.2 Prostate Re-biopsy**

- 8.2.1** The two-year biopsy will be performed for any patient who has achieved a clinical complete response (*NED*) or an equivocal disease response (*ED*) unless there is a medical contraindication to rebiopsy or definite evidence of local progression by clinical physical exam.
- 8.2.2** If the patient has distant metastatic disease or is post orchiectomy, the biopsy will not be performed.

## **9.0 OTHER THERAPY**

Not applicable to this study.

## **10.0 PATHOLOGY (4/1/95, 7/1/97, 7/14/08)**

**10.1** Central pathology review of the diagnostic and of the 2-year biopsies are planned for this study. Central reviews of previous prostate studies have demonstrated a 34% discrepancy in histological grading.

**10.2** Hematoxylin and eosin(*H & E*) stained slides and a representative tissue block of all pathologic material, the pathology report and a pathology submission form will be submitted to:

Mailing Address: For Non-frozen Specimens Only

RTOG Biospecimen Resource  
University of California San Francisco  
[name]  
[name]  
[name]

Courier Address (FedEx, DHL, etc.): For Frozen Specimens

RTOG Biospecimen Resource  
University of California San Francisco  
[name]  
[name]

Questions: [name]/[contact]; [contact]

**10.2.1** H& E stained slides will be retained until completion of the analysis of the study. Slides will be returned if specifically requested at that time.

**10.2.2** Blocks will be retained for the special studies outlined below. Slides prepared from the blocks will also be retained.

- 10.2.3** If blocks will not be released, submission of 10 unstained sections mounted on sialinized (*or other "sticky slides"*) may be substituted.
- 10.3** All pretreatment biopsies will be assessed for the presence of tumor and graded according to Gleason (*see Appendix V*).
- 10.4** DNA content and proliferation rate will be assessed in all cases by image analysis (*Feulgen staining*) and immunocytochemistry (*MIB-1 antibody*).
- 10.5** Pretreatment biopsies of patients randomized to receive hormone ablation will be evaluated for expression of the bcl-2 proto-oncogene by immunohistochemistry. Overexpression of bcl-2 has been found to correlate with hormone resistance. In this study, the potential value of bcl-2 as a predictor of hormone resistance will be studied.
- 10.6** Post-treatment biopsies will be assessed for the presence of persistent tumor.
- 10.6.1** All positive biopsies will be histologically graded according Gleason and the degree of therapy effect in the tumor cells will be graded according to Dhom and Degro.
- 10.6.2** In cases where there is difficulty in diagnosis, immunohistochemical staining for high molecular weight cytokeratin will be performed to aid in the distinction of atypical benign glands from carcinoma.
- 10.7** To encourage compliance, your Pathology Department can be reimbursed for obtaining blocks or cutting slides.
- 10.8** Patient consent form should give the Pathology Department authority and responsibility to comply with this request (*pathology blocks belong to the patient from whom tissue has been removed*).

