## **13.0 Statistical Considerations**

### **13.1 Study Design**

The objectives of the trial are described in Section 2.0. They can be met by a randomized comparison of two groups testing neoadjuvant total androgen suppression (*TAS*) before/during RT versus RT alone.

Treatment allocation will be done by randomized permuted blocks within strata to balance for prognostic factors. Stratification will be done by PSA (< 4, 4-20) and differentiation (*well*, *moderate*, *poor*), and nodal status (*N0*, *NX*).

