## 13.4 Analysis Plan (11/13/00) (11/17/05) (7/14/08)

Analyses of time to treatment failure will use the log-rank test and the Cox proportional hazards model. All hypothesis testing will be two-sided. Exploration of the effects of pretreatment prognostic factors such as stage, Gleason score and PSA will be done using the Cox proportional hazards model. There will also be exploratory analyses of the different reasons for treatment failure.

Interim accrual and morbidity reports will be done at least semi-annually prior to the RTOG group meeting. The report will describe accrual by institution and project completion of accrual. It will give the distribution of pretreatment characteristics and a tabulation of toxicities.

Three interim treatment comparisons shall be performed when we observe 29%, 60% and 80% of the 261 required maximum number of prostate cancer related deaths. The first interim analysis is projected to take place at the second year after the closure (*every patient has at least one year of follow-up*). The second and third interim analyses are projected to take place at the fifth year (*4 years of follow-up*) and seventh year (*6 years of follow-up*) after the closure, respectively. For each of these interim analyses, toxicity, treatment delivery and efficacy statistics will be reported to RTOG DMC. The boundary for early stopping (*or the nominal significance level for the test*) will be computed based on the observed number of deaths according to the O'Brien-Fleming alpha spending function approach. If the difference is highly significant, i.e., p value less than the

nominal level, the responsible statistician will recommend to DMC that the study be written up for publication.

Analysis of SAQ will be performed on all patients that complete baseline questionnaires. The analysis will utilize analysis of variance, and repeated measures analysis of variance to examine differences in treatments. SAQ will be examined for responsiveness in follow-up and correlation to changes in serum testosterone. Analysis of SAQ by subgroups will be undertaken for groups with sufficient sample size.

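### bcl-2 is stained only in the hormone arm, so for any failure endpoint after RT the plan cannot separate hormone resistance from prognosis or radioresistance

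*Protocol*

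**What the plan says.** Section 10.5 limits the assay by randomized arm: "Pretreatment biopsies of patients randomized to receive hormone ablation will be evaluated for expression of the bcl-2 proto-oncogene by immunohistochemistry". The stated purpose follows: "In this study, the potential value of bcl-2 as a predictor of hormone resistance will be studied".

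The restriction is deliberate rather than loose wording, because section 10.4, immediately before it, covers both arms for the other markers: "DNA content and proliferation rate will be assessed in all cases by image analysis", with MIB-1 by immunocytochemistry.

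Tissue is requested without regard to arm. Section 10.2 asks for "a representative tissue block of all pathologic material", and section 10.2.2 adds that "Blocks will be retained for the special studies outlined below". Where blocks are refused, section 10.2.3 accepts unstained sections.

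The design in section 13.1 is a "randomized comparison of two groups testing neoadjuvant total androgen suppression" before and during RT against RT alone. bcl-2 does not appear in the objectives (2.0), the endpoints (13.2) or the analysis plan (13.4). The exploratory Cox analyses there name other factors: "Exploration of the effects of pretreatment prognostic factors such as stage, Gleason score and PSA will be done using the Cox proportional hazards model". Hormone resistance is not defined anywhere.

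**The concern.** A marker of hormone resistance should identify men in whom adding TAS achieves less. That is a statement about how the TAS effect differs by marker status, and it needs marker status in men with and without TAS. Section 10.5 reads the marker only in men who had both TAS and RT. If bcl-2-positive men in Arm 1 fail sooner, three explanations fit equally well: resistance to hormones, resistance to radiation, or a more aggressive tumour whatever the treatment.

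Arm 2 is the randomized contrast that would distinguish the first explanation from the other two, and for this question it is not used. A statistical analysis plan cannot make this good, because section 10.5 settles which specimens are assayed. The risk is that an ordinary prognostic association is reported as prediction of hormone resistance.

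**Working it through.** The protocol gives no sample size, power or error rate for bcl-2, so there is no stated figure to reproduce. The check has three parts.

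**1. Identifiability.** Let P be the prognostic hazard ratio (HR) of bcl-2 without TAS and I the bcl-2-by-TAS interaction HR.

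- Marker HR in Arm 1 = P × I
- Marker HR in Arm 2 = P

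Arm 1 alone gives one observable for two unknowns. Example with an assumed Arm 1 marker HR of 1.5:

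| | P | I | Arm 1 marker HR | Arm 2 marker HR |
|---|---|---|---|---|
| Purely prognostic | 1.5 | 1.0 | 1.5 | 1.5 |
| Purely predictive | 1.0 | 1.5 | 1.5 | 1.0 |

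The two cases differ only in the arm that is not stained. What that hides can be shown with the section 13.4.1 hazards (0.0639 in Arm 2, 0.0501 in Arm 1, ratio 0.784) and an assumed 20% positive.

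- Prognostic case: Arm 2 marker-negative hazard = 0.0639/(0.8 + 0.2 × 1.5) = 0.0581. Arm 1 hazards = 0.784 × 0.0581 = 0.0455 (negative) and 1.5 × 0.0455 = 0.0683 (positive). The TAS HR is 0.784 in both marker groups.
- Predictive case: the same Arm 1 hazards, but 0.0639 for both groups in Arm 2. The TAS HR is 0.0455/0.0639 = 0.71 in negatives and 0.0683/0.0639 = 1.07 in positives.

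Identical Arm 1 data thus fit a uniform TAS benefit and no benefit in marker-positive men.

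**2. How often a purely prognostic marker would look important in Arm 1.** Inputs: 1980/2 = 990 men per arm; first-failure rate 0.12 per year (section 13.3, a planning average from other datasets); a 33% reduction (the target in section 13.3). Assumptions not in the protocol: five years of follow-up, 20–30% positive, marker HR 1.5 or 1.3.

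- No reduction: 990 × (1 − exp(−0.12 × 5)) = 447 failures, taken as 430.
- 33% reduction: 990 × (1 − exp(−0.0804 × 5)) = 328, taken as 326.

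Power = Φ(ln HR × √(D × p × (1 − p)) − 1.96), where D is the number of typed failures and p the positive share. For D = 430, p = 0.2, HR 1.5: 0.405 × 8.295 = 3.36, and Φ(1.40) = 0.92.

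| Arm 1 scenario | D | HR 1.5 | HR 1.3 |
|---|---|---|---|
| No reduction, all typed | 430 | 92–97% | 59–70% |
| 33% reduction, all typed | 326 | 83–92% | 47–58% |
| No reduction, half typed | 215 | 66–78% | 34–42% |
| 33% reduction, half typed | 163 | 54–66% | 27–34% |

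Ranges run from p = 0.2 to p = 0.3. No allowance is made for the 10% unevaluable cases in section 13.8.2. An interaction test on the same marker would be positive about 5% of the time, which is simply its significance level.

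**3. What two-arm staining could detect.** With D1 and D2 typed failures in the two arms, SE = √((1/D1 + 1/D2)/(p(1 − p))) and power = Φ(ln 1.5/SE − 1.96).

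| Staining | D1 (Arm 1) + D2 (Arm 2) | Power, interaction HR 1.5 |
|---|---|---|
| Everyone, no reduction | 430 + 430 | 66–78% |
| Everyone, 33% reduction in Arm 1 | 326 + 430 | 60–72% |
| Random half, no reduction | 215 + 215 | 39–49% |
| Random half, 33% reduction in Arm 1 | 163 + 215 | 35–43% |

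Using the 716 deaths of section 13.4.1 as events instead, and 20–50% positive, gives 58–77% with all typed and 34–48% with half.

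**The case against.** Four points can fairly be made for the plan.

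- **The aim is modest.** The text says that a potential value will be studied. It names no test, endpoint or decision rule, and bcl-2 stands outside the objectives and endpoints. This stands, and it is why severity is low.
- **One readout needs no Arm 2 tissue.** A reader might infer that one-arm staining makes the whole aim unanswerable. The protocol does not support that. Section 11.1 schedules PSA pretreatment and, in Arm 1 only, at the start of XRT, after about two months of TAS and before any RT. A bcl-2 association with that PSA fall is not mixed with radiation response. However, the protocol does not link this PSA to bcl-2, and section 13.3 cautions that TAS lowers PSA and that time to initial PSA failure may not indicate clinical outcome.
- **Nothing is lost for good.** A reader might infer that the control group has been thrown away, or that men could be steered from TAS on the result. Tissue is requested from all patients and blocks are retained, so Arm 2 can be stained later, and nothing in the protocol lets bcl-2 guide treatment.
- **The percentages depend on the inputs.** The 0.12 rate belongs to the sample-size text for 670 patients, and marker prevalence and effect are assumed. This stands. The identifiability argument uses none of these numbers.

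It is also tempting to call second PSA failure the plan's measure of hormone resistance and to fault the omission of Arm 2 on that ground. Section 11.3.7 speaks only of relapse therapy, and section 13.7 treats the endpoint as a possible surrogate for prostate cancer death, so that label would be the reader's own.

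**Conclusion.** The point holds for failure and survival endpoints after RT. There, Arm 1 data alone cannot distinguish hormone resistance from general prognosis or radioresistance, and neither more patients nor longer follow-up changes that. It does not hold for a response measured under TAS before RT.

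Under the stated assumptions, a purely prognostic marker with HR 1.5 would give a significant one-arm result in about 83–97% of trials. The position in that range depends on the positive share and on whether TAS lowers the 0.12 yearly failure rate by 33%. With half the tissue usable it falls to about 54–78%, and smaller effects lower it further. These are illustrations, not estimates for this trial.

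Severity is low. The primary comparison of overall survival is unaffected.

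**What to change.** Amend section 10.5 so that retained pretreatment tissue from both arms is stained for bcl-2, as section 10.4 already provides for DNA content and MIB-1. State that the predictive question is answered by the bcl-2-by-treatment interaction.

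- **Preferred: stain everyone.** This needs about twice the bcl-2 assays and gives roughly 60–78% power for an interaction HR of 1.5 under the assumptions above.
- **Fallback: stain a random half of each arm.** The assay count is unchanged, but interaction power is only about 35–50%, so a true effect of that size would more likely than not be missed. The standard error of the marker effect within Arm 1 also rises by a factor of √2, about 1.4.

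In either case, add an analysis of bcl-2 in Arm 1 against the PSA change from pretreatment to start of XRT. Those PSA values are already collected, so it needs no further assay.

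If Arm 2 is not stained, reword the aim for failure endpoints as the prognostic value of bcl-2 among men treated with TAS plus RT. That costs one sentence.

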## **11.0 PATIENT ASSESSMENTS**

### **11.1 Study Parameters (10/1/96, 7/1/97, 9/8/98, 11/13/00)**

| Parameter      | Pretreatment | At start of XRT | At end of XRT | Follow-up |
|-----------------------|---------------------|------------------------|----------------------|------------------|
| History & Physical    | X                   | X(b)                   | X                    | X                |
| Karnofsky Status      | X                   | X(b)                   | X                    | X                |
| Sexual Status         | X                   | X(b)                   | X                    | X                |
| Chest X-ray           |                     |                        |                      | X(a)             |
| Bone Scan             | X                   |                        |                      | X(a)             |
| CBC, alk. phos.       | X                   | X(b)                   | X                    | X(e)             |
| ALT                   | X                   | X(b,f)                 | X(b)                 | X(c)             |
| Serum Testosterone    | X                   |                        | X                    | X(d)             |
| Lymph Node Assessment | X                   |                        |                      | X(a)             |
| PSA                   | X                   | X(b)                   | X                    | X(g)             |
| Prostate Biopsy       | X                   |                        |                      | at 24 months     |

- As indicated
- Only in patients assigned to receive drug treatment, Arm 1.
- If abnormal following administration of drugs.
- Serum testosterone will be repeated at the time of the first follow-up in all patients. If abnormal, repeat until it returns to the normal range or at 2 years, whichever comes first. For patients assigned to Arm 1, serum testosterone levels will be done when Zoladex is terminated and at 6 and 12 months post termination.
- CBC is done at every followup for 2 years after end of treatment; alkaline phosphatase is performed yearly.
- Monthly during hormone therapy. If liver functions rise to  $\geq 2 \times$  normal, flutamide will be discontinued and [name] notified.

- g. All PSA determinations (*minimum of q 6 months*) within a followup period must be reported on the followup forms (F1); include a statement as to whether hormonal therapy was initiated for PSA or other relapse.

